### Randomization

The eligible participants will be classified into eight strata based on three factors: baseline cycloplegic SE (+0.50 D to < +1.00 D vs >-0.50 D to +0.25 D), gender (male vs female), and parental myopia (one vs two parents). All these factors are associated with myopia development. At the baseline visits, participants in each stratum will be randomly assigned in a 1:1:1 ratio to one of three groups: treatment group 1 (DIMS spectacle lenses), treatment group 2 (0.01% atropine eyedrops), or the control group (usual care). Random allocation will be conducted using a random sequence generated in Excel, with block randomization applied using a block size of 3.

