### Sample size calculation

According to previously randomized clinical trials, the 1-year mean change of cycloplegic SE with the DIMS spectacles, 0.01% atropine eyedrops, and the control group (single vision spectacles or placebo eyedrops) was -0.17 D, -0.38 D and -0.55 D, respectively [25]. The standard deviation (SD) of mean SE changes was around 0.5 to 0.7 in the abovementioned groups, so we choose 0.6 as the SD factor. To achieve 80% power, a significance level of 0.05, 95% CI; two-sided), and 1:1:1 allocation in a test of analysis of variance (ANOVA), the estimated sample size would be 174 participants (58 in each group) based on the calculation using the software G*Power 3.1. With the estimated dropout rate of 25% over the 1.5-year follow-up, a final sample size is 234 participants (78 in each group).

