### Statistical analysis

The database of examination parameters and questionnaire items of this study will be constructed with Microsoft Excel software (Redmond, WA, USA). Only the data from the eye with less SE (more myopic or less hyperopic) in each child will be used for identifying refractive status and ocular parameter analysis. Continuous variables will be expressed as mean (SD). Categorical variables will be expressed as frequency and percentage. The independent Student’s t-test, ANOVA, or Pearson’s chi-square test will be adopted to compare the differences between groups in terms of refractive error, demographic characteristics, and questionnaire items. Repeated measures ANOVAs will be used to test the interaction effect of time and treatment for the repeated measures during the follow-up examinations. Statistical analysis will be carried out using IBM SPSS Statistics 26 (IBM Corp., Armonk, N.Y., USA). All p values < 0.05 are considered statistically significant.

For the analysis of the primary outcome, the 1.5-year myopic shift of SE is calculated as the difference in SE between visits at baseline and at Month 18. The changes in SE over the 1.5-year follow-up period will be compared using ANOVA. The post hoc test will be carried out with Bonferroni correction to minimize the potential type I error due to multiple comparisons. The efficacy of myopic shift retardation of the therapeutic intervention is determined by dividing the difference in myopic shift between the treatment group and the control group with the myopic shift in the control group. The intention-to-treat analysis will be adopted to address the issue of loss to follow-up. The missing data in the repeated measures analysis will be dealt with generalized estimating equations (GEE). With one within-subject factor (time), one between-subject factor (treatment assignment) and their interactions, GEE will be employed to determine the treatment effect on the primary outcomes adjusted for some confounding factors, including age, gender, baseline SE, number of myopic parents, time spent on near works and outdoor activities.

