The secondary outcomes include the proportion of incident myopia, the proportion of fast myopic shift of SE, and the changes in mean axial length over the 1.5-year follow-up period. The analyses on the secondary outcomes will also be conducted with intent-to-treat principles. Using exact unconditional methods based on the Farrington-Manning score statistic, we will calculate the difference in the cumulative incidence of myopia among groups of different treatment assignment. As a binary outcome, the proportion of fast myopic shift of SE will be analyzed with Pearson’s chi-square test to compare the difference among groups. In addition, time-dependent Cox regression will be adopted to control the time-varying covariate in the analysis of the incidence of myopia and fast myopic shift of SE. Just like the analysis of myopic shift of SE, we will use ANOVA and Bonferroni correction to compare the mean change of axial length in each group. GEE will also be adapted to the treatment effect on this secondary outcome with the adjustment of the abovementioned confounding factors.

The exploratory outcomes include time to myopia onset, the changes in mean subfoveal choroidal thickness and amounts of near work/outdoor activities over the study period. In the analysis of time to myopia onset, we will assess survival analysis using a Kaplan–Meier method, with the significance based on the log-rank test. As a continuous variable, subfoveal choroidal thickness will be assessed with GEE to compare the changes among the three groups. The differences in the questionnaire items among the three groups will be estimated with ANOVA test.

The interval between the baseline visit and the last follow-up visit before school entrance is defined as “preschool stage”. The interval between the last follow-up visit before school entrance and the final visit is defined as “elementary school stage”. It is estimated that there will be nine months in both stages. The changes in SE and axial length in each stage are calculated as the difference in SE and axial length between the first and the last visits in the stage. We will use a paired t-test to compare the differences in mean change of SE and axial length between preschool and elementary school stages in each group.

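### Incident myopia is compared across three arms with a two-sample method at 0.05 and no correction, although the plan corrects the arm pairs for spherical equivalent and axial length

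*Protocol article*

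**What the plan says.** All of the following is in the protocol article.

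- **Arms** (Randomization): "participants in each stratum will be randomly assigned in a 1:1:1 ratio to one of three groups".
- **Threshold** (Statistical analysis): "All p values < 0.05 are considered statistically significant".
- **SE change, primary:** ANOVA, followed by post hoc tests with Bonferroni correction. The stated reason is type I error from multiple comparisons.
- **Axial length, secondary:** "we will use ANOVA and Bonferroni correction to compare the mean change of axial length in each group".
- **Incident myopia, secondary:** exact unconditional methods based on the Farrington-Manning score statistic, by which "we will calculate the difference in the cumulative incidence of myopia among groups of different treatment assignment". The number of contrasts is not given, and neither a three-group test nor a correction is attached.
- **Fast myopic shift, secondary:** one Pearson chi-square test among the groups. No pairwise step is described.

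**The concern.** Farrington-Manning is a two-sample statistic. Applied to three arms it yields up to three pairwise results, and the general threshold reads each of them at 0.05. For SE and axial length the plan has both an overall test and a correction of the pairs. For incident myopia it has neither, although axial length ranks at the same secondary level.

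At stake is how far a single significant pair for incident myopia can be trusted. The abstract's conclusion and the Discussion tie the trial to preventing or delaying onset and to eye care policy for premyopic preschoolers. A positive pair on this outcome would probably be quoted in support of that, yet its arm comparisons are the least protected of those described.

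**Working it through.** **What the plan gives.** It states no family-wise error rate, so there is none to reproduce. The inputs taken from it are three arms, 0.05 per test, and the arm sizes.

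**Arm sizes.** The dropout step reproduces: 58/0.75 = 77.3, rounded up to 78 per arm, 234 in total. The figure before dropout does not. The means ("was -0.17 D, -0.38 D and -0.55 D, respectively") have between-group SD √(0.0725/3) = 0.155, so with SD 0.6, f = 0.155/0.6 = 0.259. A one-way ANOVA at 0.05 and 80% power then needs 49 per arm (147), not 174. That is a separate matter. It does not enter the error rates below, which take 58 and 78 per arm as stated.

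**Assumption.** The documents give no expected incidence over 18 months in this population. A common incidence of 10% to 50% in all arms is assumed.

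**Step 1, large-sample benchmark, all arms equal**

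- Three tests, if they were independent: 1 − 0.95³ = 14.3%.
- Three pairs among three arms share data and are correlated. At least one is significant when the range of three standard normal values exceeds 1.96 × √2, which has probability 12.2%.
- Two comparisons with a shared control: 9.0%.
- Three pairs at 0.05/3 = 0.0167: 4.4%.
- One three-group test on 2 degrees of freedom: 5.0%. Testing pairs only after it is significant also gives 5.0%.

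**Step 2, the test that the plan names.** For arms with x₁ and x₂ events out of n and a null difference of zero, the score statistic is z = [(x₁ − x₂)/n] / √[2p̄(1 − p̄)/n], with p̄ = (x₁ + x₂)/(2n). The exact unconditional p value is the largest probability, over all values of the common incidence, of a |z| at least as large as the one observed. Let q be the binomial(n, p) probabilities, and let N = 1 where that p value is not below 0.05 and N = 0 otherwise. Then:

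- three pairs: error = 1 − Σ qₐ q_b q_c Nₐb Nₐc N_bc
- two pairs against control c: error = 1 − Σ q_c (Σ qₐ Nₐc)²

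Full enumeration for n = 58 and n = 78, incidence 10-50%:

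| Comparisons | At least one false positive |
|---|---|
| Three pairs at 0.05, 58 per arm | 9.8-11.3% |
| Three pairs at 0.05, 78 per arm | 11.1-12.0% |
| Two pairs against usual care at 0.05, either size | 7.2-8.9% |
| Three pairs at 0.0167, either size | 3.6-4.4% |

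The asymptotic version of the score test gives 11.1-12.9% for three pairs. The exact method is conservative, which lowers the rate somewhat but does not remove the inflation.

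**Step 3, fast myopic shift.** The planned three-group chi-square test has a simulated error of 4.6-5.1% at 58 and 78 per arm with event rates of 10-50%.

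**The case against.** The strongest reply has four parts.

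1. **The contrasts are inferred.** The sentence speaks of calculating a difference, gives no number of pairs, and sets no threshold of its own. The efficacy measure for SE compares each treatment with control, so two contrasts may be meant. This stands. The size must be given for both readings, and three pairs cannot be presented as what the plan says.
2. **The outcome is secondary, and this is a condensed article.** Multiplicity for secondary outcomes is often left to the analysis plan, which is not shown and may settle it. That limits the weight of the point. It does not remove it, because the article itself fixes a two-sample method, a 0.05 threshold for every p value, and a correction for another outcome of the same rank.
3. **Bonferroni for axial length simply follows from repeating the SE procedure.** That is fair. The plan states no general policy of correcting all secondary outcomes, so this is uneven treatment rather than a contradiction.
4. **Other analyses cover three groups.** The log-rank test for time to onset does, but it belongs to an exploratory outcome. It is not made a condition for the pairwise comparisons.

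A reader might also infer that fast myopic shift has the same inflation. The text does not support that: it describes one three-group test, which holds about 5%. A rate near 12% would arise only if three unadjusted pairwise tests were added, and none is described. Nor is 10-12% a joint rate for the two binary outcomes.

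**Conclusion.** The point holds for incident myopia only. As written, the family-wise error for its arm comparisons is about 10-12% if all three pairs are tested, or about 7-9% if only the two comparisons with usual care are made. Bonferroni over three pairs gives about 4%, and a three-group test first gives about 5%.

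These figures assume the exact unconditional test, 58 to 78 children per arm, and an equal incidence of 10-50% in all arms, which is not a figure from the documents. It would overstate the case to say that the error always exceeds twice 5%, since the lowest value for three pairs is 9.8%. The 0.05 in the plan is a per-test threshold and not a promised family-wise rate. The SE and axial length comparisons, and fast myopic shift as written, are unaffected. This is an inexpensive consistency correction to one secondary outcome.

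**What to change.** State which arm pairs will be compared for incident myopia, and then choose one of two rules:

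- **Three-group test first.** Test the three-group difference in incident myopia at 0.05, and make the pairwise Farrington-Manning comparisons at 0.05 only if it is significant. With three arms this is a closed test. If any two pairwise null hypotheses are true, all three arms are equal, so the overall test covers every case with more than one true null.
- **Bonferroni.** Apply the correction already used for axial length, 0.05/3 = 0.0167 per pair if all three pairs are tested.

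The general sentence on p values should then say that these comparisons follow the chosen rule.

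Fast myopic shift needs no change to its test. If pairwise follow-up is wanted, add that it will be made only after the three-group chi-square test is significant.

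The cost is one or two sentences, with no further participants or data. The downside is a slightly stricter criterion for pairwise claims on incident myopia.

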### Participants’ recruitment and eligibility

We intend to conduct the recruitment process from September to December 2024, during which the eye care program (the Yilan Myopia Prevention and Vision Improvement Program [YMVIP]) will take place at all kindergartens in Yilan County. The methodology of the YMVIP, involving repeated countywide population-based cross-sectional surveys in Yilan, has been detailed elsewhere [2]. Once premyopic preschoolers are identified through the cycloplegic refraction examination of the YMVIP program, their parents or guardians will be contacted and invited to participate in this trial. The inclusion criteria for this trial are listed as follows:

Age at enrollment: 5–6 years old (the senior grade of kindergarten)Cycloplegic SE of the eye with less SE (less positive or more negative refractive error): < +1.00 D and > -0.50 DAstigmatism: 1.0 D or less in both eyesAnisometropia: 1.50 D or lessMonocular uncorrected visual acuity: 6/7.5 or better in both eyesEither of the parents with moderate myopiaAcceptance of random group allocationSubmission of complete informed consent.

The exclusion criteria are listed as follows:

Strabismus or any ocular motility disorderAny ophthalmic and systemic disorders that might affect visual functions or refractive developmentPrevious treatment of atropine or other myopia control intervention

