#### DIMS spectacle lenses (Treatment group 1)

The DIMS lenses (MiyoSmart, Hoya, Tokyo, Japan) are custom-made plastic spectacle lenses [26]. In this trial, the central optical zone of the DIMS lenses is designed to have no power since the eligible participants have normal uncorrected visual acuity. Unlike the full-time wearing of DIMS spectacle lenses by myopic children, the eligible premyopic participants in this group will be instructed to wear DIMS spectacle lenses part-time until elementary school entrance or until a myopic shift of SE equal to or more than 0.50 D, whichever comes first. In part-time mode, subjects are asked to wear DIMS spectacle lenses after school hours and during weekends and holidays, especially when doing near work. Wearing the spectacles during school hours is not compulsory in the part-time mode. After either entering elementary school or experiencing a myopic SE shift of 0.50 D or more in either eye, the participants will transition to wearing the DIMS spectacles full-time, except during sleep and showers, until the end of the trial. At spectacle dispensing and at each follow-up visit, study staff will provide face-to-face instructions to the subjects and their parents, guardians, or caregivers about the details of spectacle care and the wearing regimen. The use of topical atropine of any concentration will not be permitted for any subject in the DIMS group during the study period.

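### Preschool and elementary school changes are compared as raw within-arm differences over stages that need not be equally long; annualise them and add a contrast with control

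*Protocol article*

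**What the plan says.** The last paragraph of Statistical analysis in the protocol article defines two stages. For the first: "The interval between the baseline visit and the last follow-up visit before school entrance is defined as “preschool stage". For the second: "The interval between the last follow-up visit before school entrance and the final visit is defined as “elementary school stage". The length is given as an expectation: "It is estimated that there will be nine months in both stages". Change within a stage is a plain subtraction of first from last visit, with no division by time. The test is then fixed: "We will use a paired t-test to compare the differences in mean change of SE and axial length between preschool and elementary school stages", carried out within each arm.

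Three other sections bear on this.
- Participants' recruitment and eligibility: "We intend to conduct the recruitment process from September to December 2024".
- Follow-up schedule: visits fall every three months to month 18, and most participants (not all) are expected to enter school after the first nine months.
- DIMS spectacle lenses (Treatment group 1): wear changes from part-time to full-time "After either entering elementary school or experiencing a myopic SE shift of 0.50 D or more in either eye".

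The Discussion names the comparison before and after school entry as an intended contribution of the trial.

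**The concern.** A paired test on raw changes answers the school-entry question only if the two stages are equally long. If they are not, a child whose refraction drifts at a constant rate shows more change in the longer stage, and the test can read this as an effect of school entry. The second stage also begins before entry, so some preschool time is counted as elementary school time.

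Two further points limit what the tests can show. Separate tests in each arm do not show whether the before/after difference varies between arms: significance in one arm and not in another is not evidence of a difference. In the DIMS arm, the event that divides the stages also changes the wearing mode, so a within-arm result there cannot be read as an effect of school entry. What is at stake is the interpretation of a stated aim, not the main efficacy result.

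**Working it through.** **Inputs from the protocol article.** Four-month recruitment window, September to December 2024 (Participants' recruitment and eligibility). Visits at months 3, 6, 9, 12, 15 and 18 (Follow-up schedule). One-year SE changes of -0.17 D (DIMS), -0.38 D (atropine) and -0.55 D (control), and 58 per arm before the dropout allowance (Sample size calculation).

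**Assumptions, not in the document.** Baseline visits spread evenly over the 122 days from 1 September to 31 December 2024. One common school-entry date, varied from 1 August to 1 October 2025. A constant rate of change within each child.

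**Step 1: the plan's nine months.** A 9/9 split arises when month 9 is the last visit before entry, so that month 9 falls before entry and month 12 does not. Baseline must then lie 9 to 12 months before entry, a span of three months. The recruitment window is four months, so at most about 3/4 = 75% of evenly spread baselines qualify. The nine-month figure is reproduced for those children but not for all.

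**Step 2: split by entry date.** Mean preschool length = 9 + 3 x (share 12/6) - 3 x (share 6/12). Elementary length = 18 minus that. Spurious difference (extra myopic shift in the elementary stage) = rate/12 x (elementary months - preschool months).

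| Entry date | 9/9 | 6/12 | 12/6 | Mean months, preschool / elementary | At 0.55 D/year | At 0.38 D/year |
|---|---|---|---|---|---|---|
| 1 Aug | 50% | 50% | 0 | 7.50 / 10.50 | +0.138 D | +0.095 D |
| 1 Sep | 74.6% | 25.4% | 0 | 8.24 / 9.76 | +0.070 D | +0.048 D |
| 15 Sep | 74.6% | 13.9% | 11.5% | 8.93 / 9.07 | +0.007 D | +0.005 D |
| 1 Oct | 75.4% | 0 | 24.6% | 9.74 / 8.26 | -0.068 D | -0.047 D |

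Example, 1 September: children with a December baseline (31/122 = 25.4%) reach month 9 on or after entry, so their cut is month 6. The mean preschool length is 9 - 3 x 0.254 = 8.24 months, and 0.55/12 x (9.76 - 8.24) = 0.070 D. For a single 6/12 child the difference is 0.55 x (12 - 6)/12 = 0.275 D.

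**Step 3: effect on the test.** With 25% of children at 6/12, the mean artefact at 0.55 D/year is 0.25 x 0.275 = 0.069 D. With n = 58 and an assumed SD of the paired difference of 0.4, 0.6 or 0.8 D, a nominal 5% paired t-test rejects in about 25%, 14% or 10% of trials when there is no school effect (noncentral t).

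**Step 4: preschool time inside the elementary stage.** Over the same entry dates, the gap from the last pre-entry visit to entry averages about 39 to 55 days and reaches 92 days.

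**Step 5: DIMS arm.** Suppose part-time wear keeps a fraction k of the full-time benefit (an assumption). Even with equal nine-month stages and no school effect, the regimen change alone moves the stage difference by 0.75 x (0.55 - 0.17) x (1 - k). This is 0.21 D for k = 0.25, 0.14 D for k = 0.50 and 0.07 D for k = 0.75, each towards less shift after entry. Children who switch early do so because of their own SE shift, so preschool wearing mode also depends on the outcome.

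**The case against.** The strongest reply is that the interval argument rests on premises the document does not give. No entry date is stated, the spread of baseline visits within the recruitment window is not stated, and the text already hedges by saying that nine months is estimated and that most participants enter after nine months. This stands. A reader might infer that the plan is bound to show false acceleration after school entry. The document does not support that, since the artefact is near zero for mid-September entry and reverses for 1 October.

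A reader might also set the 0.07 D artefact against the 0.17 D planned difference between atropine and control (0.55 - 0.38) and conclude that treatment effects are distorted. That comparison is mismatched: the artefact lies within an arm, and randomisation should make interval lengths similar across arms.

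A third reply is that the aim in the Discussion is a before/after comparison, and that the repeated-measures ANOVA and GEE already compare trajectories between arms. This is partly right. The document does not promise to test whether an intervention modifies the school-entry effect, but those models do not use the stage cut, so nothing planned compares arms on it.

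Finally, the stepwise DIMS regimen is deliberate and openly described. It is not an error, and no reanalysis can separate it from school entry. What remains is a limit on interpretation.

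**Conclusion.** The point holds in a limited form. The document itself fixes raw changes, a cut at the last visit before entry and within-arm paired t-tests, so this is not a detail left open for an analysis plan. If baselines spread evenly over the recruitment window and entry is on one date, about a quarter of children or more would have unequal stages. The control-arm comparison would then carry an artefact between about +0.14 D and -0.07 D for entry between 1 August and 1 October. If baseline visits fell within three months suitably placed before entry, the artefact would vanish. The stage boundary, the lack of a stage contrast between arms and the DIMS overlap do not depend on any date.

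Priority is modest: the stage comparison is not a listed primary, secondary or exploratory outcome, and the randomised comparison of 18-month change is unaffected.

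**What to change.** 1. Express each stage change as an annualised rate (D/year, mm/year) from actual visit dates. This takes the constant-rate artefact to zero. Alternatively, fit the repeated-measures model with actual time and a slope change at each child's school entry. This also assigns the weeks before entry to the right side of the boundary, which annualising alone does not.
2. Add the arm-by-stage contrast of each intervention with control, and keep the within-arm results descriptive. Apply it to rates rather than raw changes, because the raw artefact scales with each arm's rate (for 1 September entry, 0.070 - 0.048 = 0.022 D would remain between control and atropine).
3. State that in the DIMS arm the stage result, and its contrast with control, is the combined effect of school entry and the change in wearing mode, with some children switching earlier after a shift of at least 0.50 D.

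The cost is analysis wording, plus keeping visit dates and, for the model, each child's school-entry date in the database. Visits, treatment and sample size do not change.
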